### Allocation

11.1

After completion of the baseline assessment (T1), participants will be randomly allocated to the control or intervention arm. The allocation sequence will be created using computer-generated random numbers on a 1:1 ratio without stratification. Randomisation will be conducted in blocks of four, the details of which will be unavailable to research team members who enrol participants in the respective study arms.

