### Blinding

11.2

Due to the nature of the intervention, participants cannot be blinded to treatment allocation. All members of the research team will be blinded except for two research assistants (RAs). The unblinded RAs will be responsible for enrolling participants, assigning participants to the control or intervention arms according to the treatment allocation sequence generated through the software Research Electronic Data Capture (REDCap, Version 8.5.19, Nashville, Tennessee, USA), informing participants of the requirements of being in the respective study arm, advising participants in the intervention arm if they have met their weekly bus trip target and the subsequent weekly target, coordinating clinic assessments and overall be the main contact point for participants. The unblinded RAs will not be involved in conducting the post randomisation clinic assessments at T2 and T3 or data analysis. The research team member who creates the randomisation sequence will have no contact with participants and will not be involved with data collection or analysis. There are no foreseen circumstances by which unblinding of other research team members would need to occur.

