
**Table 2 tbl2:** Stepped levels of assessment participation.

Level of assessment	Survey	Smartcard data	Accelerometer	*trips4health* app	Physical measures
Minimum	✓	✓	✓		
Medium	✓	✓	✓	✓	
	✓	✓	✓		✓
High	✓	✓	✓	✓	✓

Physical measurements (blood pressure, height, weight, waist circumference) will be taken and accelerometers (ActiGraph GT3X and GT3X+) administered at the clinic assessments. All clinic assessments will be conducted at a single clinical research facility. To ensure high quality data collection, respective research team members will be trained according to standardised protocols. Height will be measured using a fixed stadiometer to the nearest 0.1 cm, and weight measured to the nearest 0.1 kg. Waist circumference will be measured at the level of the narrowest point between the lower costal (10th rib) border and the iliac crest using a Figure Finder tape measure. Three blood pressure readings at 1-min intervals will be taken after 5 min of rest (feet flat on the floor, legs uncrossed, back supported, shoulders and arms relaxed, forearms resting on chair/table) using an automated Omron HEM 907 blood pressure device.

Participants will be asked to wear a wrist-worn accelerometer for seven consecutive days, as recommended [41]. Accelerometers accurately and reliably measure step count, PA frequency, intensity and duration and sedentary behaviour [[42], [43], [44]]. Accelerometers will be issued where possible at clinic assessments, but for those unable or unwilling to attend a clinic, accelerometers will be mailed to participants in padded postage packs with instructions provided via telephone. As well as verbal instructions, all participants will receive detailed written instructions for wearing the accelerometer including monitor placement, how to return the monitor via a reply-paid padded postage pack and contact details of the study team, and a brief diary for noting the date of wear and any notable comments (e.g. unwell, forgot to wear). Monitors not returned will be followed up via telephone and email until received.

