Economic Evaluation: Non-research related resources associated with the implementation of the intervention will be documented and the comparative costs and benefits of the intervention relative to the control group will be assessed. The primary outcome of the economic analysis is a cost comparison between intervention and control groups, that is, a cost-benefit analysis with all costs and benefits expressed in monetary (AUD$) terms.

Modelled analyses will be undertaken to assess the financial implications of broader implementation rollout and intervention upscaling. Personal time (e.g. more/less time spent commuting), productivity and outlay (e.g. walking equipment, fuel, parking) costs will also be evaluated.

Process Evaluation: This will assess the fidelity and quality of implementation, clarify causal mechanisms and identify contextual factors associated with outcome variation [49]. Using the Medical Research Council UK's framework [50] designed for examining complex public health interventions, intervention acceptability at completion of the intervention will be assessed (T2) through face-to-face or telephone interviews with intervention group participants (n = 20 or until saturation of major themes) who did and did not reach bus trip targets. Participants in the intervention arm will be asked if they are willing to participate in an interview when completing the survey at T2. Interviews will be timed to coincide with clinic attendance. The recruitment and implementation impact for the public transport provider will be determined through face-to-face interviews or group discussion with key personnel (n = ≤5) at key points during the implementation of the intervention (i.e. intervention development, mid-intervention and intervention completion). Process evaluation items will be included in all three surveys for all intervention group participants.

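### Acceptability interviews in the intervention arm only are tied to the T2 clinic visit: an avoidable risk to assessor blinding and of a small one-arm reaction just before the step measurement

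*Protocol article*

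**What the plan says.** All references are to the protocol article.

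- **Who is interviewed and when (section 12.3, Process Evaluation).** Acceptability is assessed at T2 through "face-to-face or telephone interviews with intervention group participants (n = 20 or until saturation of major themes"), sampled to include people who met their bus trip targets and people who did not. Willingness is asked in the survey: "Participants in the intervention arm will be asked if they are willing to participate in an interview when completing the survey at T2". On scheduling: "Interviews will be timed to coincide with clinic attendance".
- **Who is blinded (section 11.2).** Everyone on the research team except two research assistants. Those two coordinate the clinic assessments and are the participants' main contact, but they do not conduct the T2 and T3 assessments. The section ends: "There are no foreseen circumstances by which unblinding of other research team members would need to occur".
- **What happens at the visit (section 12.1).** Blood pressure, height, weight and waist are measured, and accelerometers are "administered at the clinic assessments", or mailed to those who cannot or will not attend. Wear is for seven consecutive days. All clinic assessments take place at one facility.
- **Primary endpoint (section 8).** Accelerometer average daily steps at T2 (week 17 or 18).
- **Process items in the surveys (section 12.3).** "Process evaluation items will be included in all three surveys for all intervention group participants". Section 11.1 says: "After completion of the baseline assessment (T1), participants will be randomly allocated to the control or intervention arm".

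**The concern.** The interview is an event that only one arm can have, and the plan attaches it to the visit where two things should be the same in both arms: the assessor's knowledge of the participant, and the circumstances in which the accelerometer wear begins.

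Two things are at stake. First, anyone at the clinic who sees that a participant is there for an interview can infer the arm. Second, for clinic attendees a conversation about the intervention falls on the visit from which the primary-endpoint wear week starts, with no matching contact in the control arm. If the conversation changes behaviour that week, part of the measured difference reflects the evaluation and not the intervention.

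A smaller matter sits in the same paragraph. Survey items meant for the intervention group are promised at all three timepoints, but at T1 no such group exists.

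**Working it through.** **1. Order of events, from the text.** T2 interview with intervention participants, coinciding with clinic attendance (12.3). T2 measures at that visit by staff other than the two unblinded assistants (11.2). Accelerometer issued at that visit where possible, then worn for seven days (12.1). Those days give the primary endpoint (8). For attendees, the wear therefore follows the visit to which the interview is tied. The order of interview and physical measures within the visit is not given.

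**2. Who could hold the interview.** The article does not say. There are two cases within the research team:

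- A currently blinded member interviews. That person then knows the participant's arm, which conflicts with the statement that no such unblinding is foreseen.
- One of the two unblinded assistants interviews. Blinding is kept only if assessors do not notice who has an interview. No safeguard is stated.

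**3. Which outcomes assessor knowledge could reach.** Steps are recorded by device and are not assessor-judged. Blood pressure is taken by an automated device. Waist is measured by tape and is the most exposed. It is a secondary outcome, and the physical measures are optional under the stepped scheme (Table 2).

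**4. Possible size of a reaction in steps.** There is no figure in the plan to reproduce on this point. Inputs:

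- Interviewees: m = 20 (section 12.3). The number is open-ended, so m = 30 is also tried, as an assumption.
- Arm size with 1:1 allocation (11.1): 300/2 = 150 analysed, or 350/2 = 175 recruited (section 9).
- Target difference: 624 steps/day (section 9), used only as a yardstick.
- Change per interviewee in the wear week, b: not in the documents. Assumed range 250 to 1000 steps/day, in either direction.

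Shift in the arm mean = (m / arm size) × b. The share interviewed is 20/150 = 13.3% or 20/175 = 11.4%.

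| m | Arm size | b = 250 | b = 500 | b = 1000 |
|---|---|---|---|---|
| 20 | 175 | 28.6 (4.6%) | 57.1 (9.2%) | 114.3 (18.3%) |
| 20 | 150 | 33.3 (5.3%) | 66.7 (10.7%) | 133.3 (21.4%) |
| 30 | 175 | 42.9 (6.9%) | 85.7 (13.7%) | 171.4 (27.5%) |
| 30 | 150 | 50.0 (8.0%) | 100.0 (16.0%) | 200.0 (32.1%) |

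Cells are steps/day, with the share of 624 in brackets. With 20 interviewees the range is about 29 to 133 steps/day, or 5% to 21%. These figures suppose that every interviewee is interviewed before wear. Any interview held after wear lowers them.

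**5. Survey items.** The survey is given at T1, T2 and T3 (section 8), and allocation follows completion of T1 (11.1). Items can be directed to the intervention group only at T2 and T3.

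**The case against.** The case on the other side is substantial, and much of it stands.

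- **No breach of blinding is stated.** A reader might infer that the plan exposes allocation to its assessors. The article does not say that assessors conduct, hear or learn of the interviews. The two unblinded assistants are not barred from interviewing, telephone interviews are allowed, and willingness is asked in the survey and not by the assessor. A condensed article may leave the interviewer's identity to the full protocol. What remains is the scheduling sentence itself, which the article does state and which creates the risk.
- **The topic is acceptability.** A reader might take the interviews to be about whether targets were met. That phrase describes who is sampled.
- **A reaction is conjecture and its direction is unknown.** Interviewees already know their arm and have had 16 weeks of targets, weekly emails and 28 text messages. Both arms answer T2 survey questions on travel and activity. One interview may add little. It is tempting to say that the bias favours the intervention, but nothing in the documents supports a direction, and people who missed their targets are deliberately included.
- **The upper assumptions are large.** A change of 500 to 1000 steps/day after one conversation would be 80% to 160% of the whole target difference (500/624 and 1000/624). At 250 the shift is about 5% of it.
- **The T1 wording may be loose drafting.** It could mean that everyone answers at T1 and that the items are used for the intervention group. It has no bearing on blinding or on the primary outcome.

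These points limit the size of the problem. They do not remove the one-arm event from the visit that precedes the primary measurement.

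**Conclusion.** The point holds as a cheap improvement, not as a demonstrated error. The schedule creates an avoidable, arm-specific risk of two kinds: assessors may learn allocation, which bears mainly on tape-measured waist, and a minority of the intervention arm (about 11% to 13% with 20 interviewees) may react just before the step measurement.

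The shift of 29 to 133 steps/day rests wholly on the assumed 250 to 1000 steps/day per interviewee and on all 20 being interviewed before wear. Only a very large individual reaction would matter materially for the primary comparison. A reader might go further and conclude that the primary result is compromised by assessor unblinding. The documents do not support that, because steps are device-recorded.

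The survey wording is a real but minor inconsistency, which would not merit a comment on its own.

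**What to change.** In section 12.3, replace the sentence that ties interviews to clinic attendance. State instead that an unblinded research assistant holds them, by telephone (already allowed) or away from the assessors, after the participant's T2 measures are complete and the T2 accelerometer has been returned.

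In the same paragraph, reconcile the survey sentence with section 11.1: intervention-specific process items can be directed only at T2 and T3.

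The cost is protocol wording and scheduling. The downside is that interviews take place one to two weeks later, so recall is slightly less fresh and the convenience of a single visit is lost. Sample size, measures and analysis are unaffected.

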## Monitoring

13

### Data monitoring

13.1

*trips4health* is a behaviour change study that does not require participants to undertake risky clinical procedures or medication regimens. For this reason, a Data Monitoring Committee was considered unnecessary, likewise the development of an interim analysis plan and stopping guidelines.

### Harms

13.2

PA intervention studies pose minimal risk to participants [51]. Although unlikely, the most common PA intervention study-related adverse events are minor musculoskeletal injuries [51]. Adverse events reported to members of the research team will be logged in REDCap, reviewed by the chief investigator to determine the appropriate action and reported to the relevant ethics committee.

At study completion, participants will be provided with a feedback letter summarising their health information (including PA, body mass index, waist circumference, blood pressure). Participants will be encouraged to share this summary information with their health care practitioner, especially if values are outside normal limits. Participants will only be provided with information about their health at the clinic assessments if their blood pressure exceeds 140/90 mmHg and under such circumstances they will be encouraged to see their health practitioner.

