**Methods:**

*trips4health* is a single-blinded randomised controlled trial with a four-month intervention phase and subsequent six-month maintenance phase. Participants will be randomised to: an incentives-based intervention (bus trip credit for reaching bus trip targets, weekly text messages to support greater bus use, written PA guidelines); or an active control (written PA guidelines only). Three hundred and fifty adults (≥18 years) from southern Tasmania will be recruited through convenience methods, provide informed consent and baseline information, then be randomised. The primary outcome is change in accelerometer measured average daily step count at baseline and four- and ten-months later. Secondary outcomes are changes in: measured and self-reported travel behaviour (e.g. PT use), PA, sedentary behaviour; self-reported and measured (blood pressure, waist circumference, height, weight) health; travel behaviour perspectives (e.g. enablers/barriers); quality of life; and transport-related costs. Linear mixed model regression will determine group differences. Participant and PT provider level process evaluations will be conducted and intervention costs to the provider determined.

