## Interventions

7

The *trips4health* study has a four-month intervention phase followed by a six month maintenance phase (Fig. 2). While there is debate in the literature about the minimum length of time needed for habits to form [29] a four-month intervention phase was selected as it allows three months for behaviour change to reach automaticity and one month for maintenance or ‘tapering off’, where contact and support is gradually withdrawn in preparation for intervention cessation [30] (Table 1). Using a ‘gain-framed’ approach (i.e. rewarding positive behaviours), participants in the intervention group will have bus trip targets from weeks 1–16 which escalate over the course of the intervention so that targets become more difficult to reach but incentive values increase. If the bus trip target is met (confirmed through objective smartcard data), participants receive bus trip credit (through their smartcard). The credit received will be commensurate with the participant's default/usual fare type that they were required to set when applying for their smartcard. The price range (AUD$) of the different fare types is $1.92 to $5.76 (a concessional fare through to a full-fare with travel across multiple zones). The maximum credit a participant can receive by the end of the 16-week intervention phase is $103.68 if travelling on a concessional fare and if travelling on a full-fare either $151.20, $207.36 or $311.04 as per their default fare type. Participants will be notified by a weekly email whether they have met or have not met their target, the smartcard credit they have received (if any) and the following week's target. Participants will be aiming to achieve five one-way bus trips per week by the end of the intervention. To assist participants to achieve the weekly targets and, consistent with best practice, incentives will be supported by other behaviour change techniques (e.g. information on consequences of behaviour to the individual, setting graded tasks, goal setting, social support), delivered via weekly mobile text messages [31]. Development of the text messages was underpinned by the Behaviour Change Technique Taxonomy, informed by our previous qualitative work on transport behaviour and PA and from an incentive-based study designed to increase weekly leisure-time PA and reduce sitting time [14,22,32]. Text messages will be offered to the intervention group only. This can help to counter the potential risk that incentives alone may undermine intrinsic motivation in the absence of broader behavioural support. It has been argued that incentives aimed at addressing habitual behaviours such as physical inactivity may be more impactful if delivered as part of effective behaviour change programs [31]. Both the intervention and control groups will receive printed versions of Australia's Physical Activity and Sedentary Behaviour Guidelines [33]. Educational materials have been selected as an active control to help engage and retain the control group – alone, this type of cognitive strategy is unlikely to influence PA behaviour [34]. All intervention support will be provided by a member of the research team.

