
**Table 1 tbl1:** *trips4health* intervention schedule.

	Intervention phase	Bus trip targets	Smartcard credit available (all zones full-fare^a^)	Smartcard credit available (all zones concessional fare^b^)	Text message frequency
Within 2 weeks pre-intervention	*Baseline survey, smartcard data, clinic assessment, accelerometer, travel behaviour smartphone app*				
Week 1	Getting started	1	$5.76	$1.92	x 2
Week 2	Getting started	1	$5.76	$1.92	x 2
Week 3	Slowly increasing	2	$11.52	$3.84	x 2
Week 4	Slowly increasing	2	$11.52	$3.84	x 2
Week 5	Moving along	3	$17.28	$5.76	x 2
Week 6	Moving along	3	$17.28	$5.76	x 2
Week 7	Moving along	3	$17.28	$5.76	x 2
Week 8	Moving along	3	$17.28	$5.76	x 2
Week 9	Aiming high	4	$23.04	$7.68	x 2
Week 10	Aiming high	4	$23.04	$7.68	x 2
Week 11	Aiming high	4	$23.04	$7.68	x 2
Week 12	Aiming high	4	$23.04	$7.68	x 2
Week 13	Keeping up	5	$28.80	$9.60	x 1
Week 14	Keeping up	5	$28.80	$9.60	x 1
Week 15	Keeping up	5	$28.80	$9.60	x 1
Week 16	Keeping up	5	$28.80	$9.60	x 1
***Total***		**54**	**$311.04** (AUD)	**$103.68** (AUD)	**28**
Week 17 or 18	*Post-intervention survey, smartcard data, clinic assessment, accelerometer, travel behaviour smartphone app*				
Week 41 or 42 >(10 months from baseline)	*Follow-up survey, smartcard data, clinic assessment, accelerometer, travel behaviour smartphone app*				

a most expensive fare type.

b cheapest fare type. 50% of the public transport provider's adult passengers travel on a concessional fare.

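### The article's Harms section states only passive capture of adverse events, while scheduled messages in weeks 1–16 go to one arm only (44 v 0); an identical item in the T2 and T3 surveys would give both arms the same opportunity to report

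*Protocol article*

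**What the plan says.** Section 13.2 (Harms) calls the risk minimal and then names what to expect: "the most common PA intervention study-related adverse events are minor musculoskeletal injuries". The one capture rule it gives follows: "Adverse events reported to members of the research team will be logged in REDCap, reviewed by the chief investigator". The chief investigator decides what to do, and the event goes on to the ethics committee. The section gives no question to be put to participants, no timetable for asking, and no procedure described as common to both arms.

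Section 7 (Interventions) and Table 1 set out the scheduled messages. On the texts: "Text messages will be offered to the intervention group only". On the emails: "Participants will be notified by a weekly email whether they have met or have not met their target". Only the intervention arm has targets, and they run for the whole phase: "participants in the intervention group will have bus trip targets from weeks 1–16". The abstract describes the comparator as "or an active control (written PA guidelines only".

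Section 12.3 adds two more channels for the intervention arm alone: interviews with about 20 members at T2, and process-evaluation items in the surveys.

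Some contact is common to both arms. Section 12.1 schedules T1, T2 and T3 for everyone. Table 2 puts the survey in the minimum level of assessment. Section 11.2 makes the unblinded research assistants the usual people for participants to approach, whichever arm they are in.

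**The concern.** When an event enters the record only because a report reached the team, the record depends on whether people think to mention it and whether there is an occasion to do so. This has two consequences.

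First, minor strains and sprains are events that people often do not volunteer. A short list could then be read as evidence of safety when it partly reflects that nobody asked. The trial is meant to inform wider rollout, so that reading matters.

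Second, scheduled contact differs by arm in the same months in which the intervention asks people to make more bus trips. If adverse events are later tabulated by arm, as trial reports commonly do, the table would mix any true difference with a difference in opportunity to report.

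**Working it through.** **1. Scheduled messages in weeks 1–16.** Inputs are from Table 1 and section 7.
- Texts: weeks 1–12 at 2 per week and weeks 13–16 at 1 per week, so 12 × 2 + 4 × 1 = 28. This matches the total printed in Table 1.
- Emails: 1 per week × 16 weeks = 16.
- Intervention arm: 28 + 16 = 44. Control arm: 0.

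The article does not state 44. It is the sum of the two schedules.

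**2. Contact shared after randomisation.** Each arm has T2 and T3. Counting these as 2 contacts, the totals are 44 + 2 = 46 against 0 + 2 = 2. The imbalance therefore lies in weeks 1–16. The roughly 20 interviews come on top, in the intervention arm only.

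**3. Do the shared assessments ask about harms?** Sections 8 and 12.1 list the survey content: demographics, travel, physical activity, health, quality of life and economic items. No injury or adverse event item is named. The accelerometer diary in section 12.1 leaves room for remarks such as feeling unwell, but it covers only the wear week. The one safety procedure described for clinic visits concerns raised blood pressure.

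**4. What unequal reporting could do.** Let the true risk p be equal in both arms, with n per arm and reporting probabilities c (control) and i (intervention). Expected logged events are n·p·c and n·p·i, so the apparent risk ratio is i/c whatever p is. Section 9 plans 350 participants and section 11.1 allocates 1:1, so n = 175. The article gives no value for p, c or i. **The values below are assumptions for illustration**, with p = 10%, so 175 × 0.10 = 17.5 true events per arm.

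| c | i | Logged, control | Logged, intervention | Apparent risk ratio |
|---|---|---|---|---|
| 0.5 | 0.5 | 8.75 | 8.75 | 1.0 |
| 0.4 | 0.6 | 7.0 | 10.5 | 1.5 |
| 0.3 | 0.8 | 5.25 | 14.0 | 2.67 |

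The last column only restates the assumed reporting rates. It shows how the bias would work and does not estimate it. The first row shows the other half of the point: with equal reporting the ratio is undistorted, yet half the events are missing from both arms.

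**5. Reading an empty log.** If none of 175 controls had an event and capture were complete, the approximate upper 95% limit for the risk would be 3/175 = 1.7%. If only 30% of events were captured (assumed), it would be about 1.7% / 0.30 = 5.7%.

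**The case against.** The strongest reply is that this section concerns monitoring, not analysis. Harms are neither an outcome in section 8 nor part of the statistical methods in section 12.3. The stated purpose of the log is to handle individual events. A reader might infer that a planned harms comparison is biased, but no such comparison is planned. This stands, and it limits the point to counts that may be reported by arm later.

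A reader might also infer that controls have no contact with the team. The document does not support that: they have T2, T3 and the research assistants. Zero is right only for scheduled messages in weeks 1–16. Nor are the 44 messages shown to be 44 chances to report. They are outbound, carrying behaviour-change content, target results and credit, and nothing says that they invite replies or ask about health. For that reason neither the direction nor the size of a bias can be asserted.

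Reports could also include answers to a question, and a journal article may leave adverse event forms to the full protocol. This is a fair caution. The article does, however, state a capture rule rather than staying silent, and the rule as stated is passive.

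Two further inferences go too far. One is that harms reporting conflicts with the blinding section. Its sentence, "There are no foreseen circumstances by which unblinding of other research team members would need to occur", is about a need to unblind. A chance remark by an unblinded participant to an assessor can occur in any conversation, and the primary outcome is device-measured. The other is that missed injuries could explain a null step-count result. No figure in the document links the two, and self-reported health and quality of life are collected in both arms at all three timepoints.

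**Conclusion.** The point holds in limited form. As stated in the article, capture of adverse events is passive, although the likely harm is a minor injury. Scheduled messages in weeks 1–16 number 44 in the intervention arm and none in the control arm, and that arm also has interviews and extra survey items. Under-recording of minor injuries is likely, and adverse event counts by arm would not rest on equal opportunity to report. The message count is exact. The effect on recorded harms cannot be quantified from the document, and its direction cannot be derived either. The conclusion assumes that no unshown survey or clinic form already asks both arms about injuries. If one does, section 13.2 only needs to say so. The primary analysis is unaffected, so this is a cheap improvement.

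**What to change.** Add to section 13.2 one identical item in the T2 and T3 surveys for both arms. It could ask whether, since the last assessment, the participant has had a fall, injury or illness that limited walking or needed care, and if so when and during what activity. Base any by-arm summary of harms on this item alone, with the number who answered as denominator. Continue to log spontaneous reports for individual follow-up, list them separately, and do not compare them between arms. Ask participants to direct such reports to the unblinded research assistants, which fits the role that section 11.2 already gives them.

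The cost is one or two survey questions at each of two timepoints and a few sentences of protocol text. The survey is already planned for every participant, so no new contact is needed. The downsides are recall over about 4 months at T2 and 6 months at T3, a higher recorded number of minor events, and no answer from participants who miss the survey.
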